## Abstract

**Introduction:**

There is insufficient evidence on the effectiveness and cost-effectiveness of psychological interventions to enhance frontline responders’ mental health proficiency and competence in emergency settings. This paper describes the methods for the evaluation of the effectiveness and cost-effectiveness of Psychological First Aid training, to determine whether the intervention is effective and cost-effective as a mental health intervention in public health emergencies. A pilot to evaluate the acceptability of the PFA training found participants were either satisfied (55.6%) or extremely satisfied (44.4%) with the training program.

**Method:**

This paper describes the protocol for a cluster randomized two-arm controlled trial. A total of 1,399 non-specialist health care workers will be recruited in 42 hospitals and health care centers across six provinces in China. Participants will be assigned according to hospital or health care center site to one of two groups (*n* = 699 for intervention group and 709 for control group) to receive system based PFA training or PFA training as usual. Both groups will receive one-day of training, comprising six modules including PFA core concepts, knowledge, skills and practice. Their knowledge, skills, competency, self-efficacy, resilience, and professional quality of life will be assessed immediately after the training; and reassessed after 1 and 2 months.

**Analysis:**

For effectiveness outcomes, repeated measures will be used in a multi-level linear mixed model. The pooled standard deviations will be used to calculate the effect sizes (Cohen’s d) within and between groups. Appropriate statistical tests will be used to explore differences between intervention and control groups. For economic outcomes, a health service sector perspective will be adopted, with intervention costs and outcomes collected prospectively. Within-trial cost-effectiveness analysis (CEA) will quantify the incremental costs and PFA proficiency gains of the intervention compared with training as usual at 2 months post training. CEA will present results as cost per unit of mental health proficiency gained. A cost-utility analysis (CUA) model will extend the population to emergency health service users.in order to identify potential for incremental cost offsets attributable to mental health improvement arising from intervention. Intervention costs and effects will be extrapolated to the population of patients who receive the emergency health service in clinical wards and will be modeled over the cohort’s lifetime. Modeled CUA results will be calculated as quality-adjusted life-years saved and healthcare cost savings in preventing mental disorders.

**Ethics and dissemination:**

Ethics approval was obtained from the Second Xiangya Hospital, Central South University Clinical Research Ethics Committee (2021) Ethical Review [Clinical Research] #067). Data about the economic evaluation of the intervention will be stored in the KCL OneDrive at King’s College London, UK. The trial protocol was registered with the China Clinical Trials Registry: ChiCTR2200060464. Study findings will be disseminated through peer-reviewed academic papers, and participating hospitals.

## Highlights

This protocol has some limitations such as the absence of emergency health service users and social perspectives about time costs and outcome measures. However it contributes to the limited number of studies of evidence on the cost-effectiveness of interventions that improve mental health proficiency for frontline health care workers.

-Data collection for the economic evaluation is prospectively planned alongside the randomized controlled trial to assess intervention effectiveness.-The cost-effectiveness study will generate important information for decision-makers, providing evidence of the “value-for-money” of the intervention.-A modeled economic evaluation will estimate the long-term potential for the cost-effectiveness of the intervention as an emergency psychological preparedness and response method.

## Introduction

Failure to address mental health issues within populations recovering from crises including natural disasters or public health emergencies can further compound economic pressures and result in higher economic losses (1). An efficient response is pivotal to coping with distress and disturbance and ensuring the quality of mental health services. As the first emergency response, non-specialist health care workers’ capacity building is a critical issue for workforce resilience and a sustainable health system. These health care workers look after affected patients and are often exposed themselves to stressful and emotional situations; they may suffer ‘moral injury’ if forced to make decisions that don’t align with their values such as witness to intense human suffering and cruelty because of the lack of resources; or have increased anxiety about becoming affected themselves and/or passing infections or diseases on to their own families. Globally, Psychological First Aid (PFA) is recommended as an evidence-informed strategy for building mental health capacity (2). Some studies conducted in emergency humanitarian settings suggest that much of the heavy social burden is caused by associated mental health disorders which may be preventable through early intervention (3). The hypothesis of this study is that the mental health capacity of non-specialist health care workers can be strengthened through a system based PFA training program. As a result, health service users will benefit from the mental health service provided by the trained health care workers.

PFA can be used to train lay people as well as health care workers. It is an easy to implement strategy for non-specialist workers. The reason we chose health non-specialist workers is that we discovered there is acute lack of psychiatrists and mental health specialists to treat people especially in disaster and emergency settings. Health frontline workers treat physical injuries and illness as well as being the first contact to the survivors. They have the potential and clinical skills to be effectively trained as psychological first aiders as recommended by World Health Organisation (4). PFA has the potential to equip non-specialist health care workers with mental health service capacity, which can be integrated into existing specialist psychological support for emergency service users. Studies suggest a need to evaluate both PFA intervention’s effectiveness and the economic consequences. However, the research evidence on the effectiveness and cost-effectiveness of PFA training for non-specialist health care workers in emergency preparedness and response is scarce (5). Only a few high-quality studies have directly evaluated psychological intervention by non-specialist healthcare workers to alleviate impacts on acute and long-term psychological well-being (6, 7). The proposed study will firstly: test the effectiveness of the adapted PFA training program for enhancing non-specialist health care workers’ mental health capacity; and secondly, measure the cost-effectiveness of the training for trainees to improve their PFA profieciency.

The Chinese PFA training program is based on a PFA Train the Trainer (ToT) manual adapted by the Psychological Rescue Institute of China Association for Disaster and Emergency Rescue Medicine (8), which includes elements of mental health awareness along with PFA training based on the Johns Hopkins University PFA guidelines (9), It is a system based program which is an integrated mental health training model. The system based training model mainly includes PFA core conception and theory courses, and practice, adding WHO guidelines, and current policies. We will compare training as usual to the CPFA system based training program. The training as usual courses are mainly based on the Mental Health Gap Action Program (mhGAP) Intervention Guide (IG) in non-specialized health settings (10) since its efficacy is already well established in the literature (11). The PFA system based training model involved six modules including PFA core conception, knowledge, skills and practice. The system based training model has been incorporated into the National Emergency Assistance Work Guideline by National Health Commission of China for training frontline responders to provide emergency psychological assistance for people affected by natural disasters and public health emergencies. The work guideline book will be published in 2022 by People’s Medical Publishing House (Accepted at Jan 13, 2022, and in press).

## Aim and objectives

### Research question

Will the PFA system based training program be effective and cost-effective in terms of the primary outcome of change in non-specialist health workers’ mental PFA proficiency, and secondary outcomes of self-efficacy, confidence and professional quality of life at two months post training?

### Hypothesis

Non-specialist health workers in the system based training arm will show superior improvement in the primary outcome in non-specialist health workers’ mental PFA proficiency. The intervention arm will also show favorable cost effectiveness.

### Objectives

The project’s overall aim is to improve the capacity of non-specialist health care workers in China to provide mental health services by applying an integrated mental health training model and thereby ultimately improve the mental well-being, resilience and health related quality of life of emergency service users.

(1). To test the effectiveness of non-specialist health care workers trained by the CPFA training program in improving their mental health capacity;

(2). To test the cost-effectiveness of a system based training model to deliver training in the Chinese PFA to build mental health capacity in non-specialist health care workers.

## Study design, participants, and setting

### Design

The study will be a two-arm, participant-blinded, cluster randomized controlled trial, comparing PFA system based training with training as usual (1:1) to improve to improve the mental health capacity of non-specialist health care workers in China over two months (eight weeks).

### Setting and participants

Hospitals will be chosen to ensure sufficient number of clusters. In China, we contacted 73 public hospitals and health centers in six provinces of Hunan, Hainan, Xinjiang, Fujian, Dalian, and Jiangxi, presented the study to their staff members, and invited them to participate. Forty-two agreed to participate. The randomization was at the hospital cluster-level which to ensure minimal contamination. The hospitals will be randomly allocated to one of two groups (the PFA training group or the control training as usual group) with a ratio of 1:1 with stratification by hospital type (primary, secondary). The randomization will be conducted by an independent administrator at CADERM not associated with the study using a block-randomization schedules provided by the study statistician. The potentially eligible subjects will be invited to participate via a text message after informed consent is obtained from all participants.

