### Randomization and allocation concealment

After the initial screening, 1,399 health care workers within 42 hospitals will be randomized in a ratio of 1:1 to either system based PFA training (intervention arm) or training as usual only (control arm). A random sequence created by the study statistician using varying block size (2 or 4) randomization technique. 21 hospitals will be allocated to the PFA system training group and 21 to the training as usual group by a senior administrator not involved in the study. Health care workers from each trial hospital will subsequently be assigned to either the control or intervention group along with their hospitals to avoid contamination. The number of participants for each trial cluster (hospital) will be approximately 33. The random allocation of the hospitals will be sent independently to the co-investigators’ email address. The email will not be sent to each study site until interventions are assigned.

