#### Repeated measures modeling

For the primary and secondary outcomes, repeated measures will be used in a linear mixed model. ANOVA with time (T0-T1-T2) as a within-groups component and treatment condition as a between-groups factor will be utilized. Mixed-model repeated measures ANOVA does not substitute missing values; it uses all the data for each participant that are available. We’ll run a sensitivity analysis to examine the effect of drop-outs on our findings. The full data sets of participants who finish all sessions of the training will be the basis for the protocol analysis. The time to onset of clinical outcomes will be based on post-training interview and two follow-up assessments. The pooled standard deviations will be used to calculate the effect sizes (Cohen’s d) within and between groups. Appropriate statistical tests will be used to explore differences between intervention and control groups (Fisher’s exact test as appropriate). The nature of the routine administrative data will determine the test’s selection. SPSS statistics, Excel, and Visual Basic for Applications will be used for all analyses (VBA).

The multilevel analysis will be used with nested data to account for clustering and adjust for the type of critical incident, age, and sex. Means and standard deviations for continuous outcomes and proportions for categorical outcomes will be reported.

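### Hospitals in six provinces are known before allocation, but the draw is balanced on hospital type only and province is not a named covariate: a valid design that leaves precision unused

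*Protocol article*

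**What the plan says.** All in the protocol article:

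- Setting and participants: "we contacted 73 public hospitals and health centers in six provinces of Hunan, Hainan, Xinjiang, Fujian, Dalian, and Jiangxi"; of these, "Forty-two agreed to participate". The list of units, and so each hospital's province, is fixed before allocation.
- Same section: hospitals are allocated "with a ratio of 1:1 with stratification by hospital type (primary, secondary"), from block schedules supplied by the study statistician. No other balancing factor is named.
- Randomization and allocation concealment: "A random sequence created by the study statistician using varying block size (2 or 4) randomization technique", and, as a fixed result, "21 hospitals will be allocated to the PFA system training group and 21 to the training as usual group".
- Repeated measures modeling: the multilevel analysis will "adjust for the type of critical incident, age, and sex". Data analysis adds demographic factors if they prove influential. Neither section names province or hospital type.
- Study procedure: all three assessments follow the training, so no pre-training score is scheduled.

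The numbers of hospitals per province and per type, and the order of the allocation list, are not given.

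**The concern.** When hospitals are the randomised units and there are only 42, the variation between them limits power. Province is a hospital-level factor that is already known and could carry part of that variation. Left out of both the draw and the model, its share stays in the error term, and chance can divide a province unevenly between arms. Age and sex act mainly at participant level and do little for the hospital-level component. With no pre-training score scheduled, nothing else in the plan would show or absorb a regional difference.

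A smaller matter is the description of the scheme. One section gives type-stratified schedules. Another gives a single sequence and an exact 21:21 split, which random blocks of 2 or 4 within two type lists do not guarantee.

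**Working it through.** **Inputs from the article.** d = 0.43, ICC 0.2, 21 hospitals per arm, 30 participants per hospital, power 0.80, 10% dropout (Sample size); alpha 0.05 two-sided (Data analysis). **Assumed, because not given:** hospitals per province, hospitals per type, list order, and the share s of between-hospital variance that province explains.

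**1. The plan's own figure.**
- Individual design: 2(1.960 + 0.842)²/0.43² = 84.9 per arm. Design effect: 1 + 29 × 0.2 = 6.8. Product: 577.3 per arm, or 577.3/30 = 19.2 hospitals.
- A normal approximation would therefore accept 20 per arm. With a noncentral t on (number of hospitals − 2) df, power is 79.5% at 20 per arm and 81.5% at 21, so 21 is the smallest number that reaches 80%.
- 1260/0.9 = 1400, against the stated 1399. The plan's figure is reproduced.

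**2. Where the variance lies.** Variance of a hospital mean (total SD = 1): 0.2 + 0.8/30 = 0.2267. Between-hospital share: 0.2/0.2267 = 88%. SE of the arm difference: √(0.2267 × 2/21) = 0.147.

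**3. How often a province splits badly** (10,000 simulated draws, types assumed 14/28, list order unrelated to province):
- 7 in each province: some province splits 6:1 or 7:0 in 42% of draws; one lies wholly in one arm in 4.6%.
- 17/5/5/5/5/5: one lies wholly in one arm in 22%.
- 12/10/8/6/4/2: the same in 55%, mostly because of the two-hospital province (20/41 = 49% by itself).
- 7 each with the list sorted by province (types 2/5 in each): 6:1 or worse falls to 2.6%.

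**4. What that does to the estimate** (7 per province). In a random 21:21 draw with c of a province's hospitals in one arm, its weight in the contrast is (2c − 7)/21, and Var(2c − 7) = 7 × 35/41 = 5.98. Over six provinces: 6 × 5.98/441 = 0.081. If s = 20%, province variance is 0.2 × 0.2 = 0.04, and the chance shift has SD √(0.081 × 0.04) = 0.057, about 0.06 SD. A single 6:1 province that deviates by one province SD (0.20) shifts the contrast by 5/21 × 0.20 = 0.048.

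**5. Power with province balanced and modelled.** Hospital-mean variance becomes 0.2(1 − s) + 0.8/30. With 7 per province the best split is 4:3, so efficiency is 12/12.25 = 0.98. SE = √(variance × 2/21 ÷ 0.98), with 40 − 5 = 35 df.

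| s (assumed) | variance | SE | power |
|---|---|---|---|
| plan, no province term (40 df) | 0.2267 | 0.147 | 0.815 |
| 0% | 0.2267 | 0.148 | 0.804 |
| 10% | 0.2067 | 0.142 | 0.839 |
| 20% | 0.1867 | 0.135 | 0.874 |
| 30% | 0.1667 | 0.127 | 0.907 |

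**6. Adjusting only after an unbalanced draw.** E[c(7 − c)] = (49 − 5.98)/4 = 10.76. Mean efficiency: 6 × (10.76/7)/10.5 = 0.88, against 0.98 with balancing.

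**7. Is 21:21 ensured?** Simulating two type lists with random blocks of 2 or 4, the last one cut at the stratum end, gives exactly 21:21 in about 50% of draws for odd strata (7/35, 11/31, 15/27, 21/21) and 78% to 79% for even strata (6/36, 10/32, 14/28, 20/22). The remainder is almost all 20:22. Power by the normal approximation is 83.3% at 21:21, 83.2% at 20:22 and 83.0% at 19:23.

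**8. Is a constrained draw feasible?** With 7 per province (2 of one type, 5 of the other), 9,261,562,500 of 143,328,588,480 type-balanced 21:21 allocations keep every province within one hospital. That is 6.5%, so ample randomness remains.

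**The case against.** The strongest reply is that omitting province is a design preference. Stratifying on hospital type alone is sound. Province variation is part of the hospital variance, so a hospital-level model's standard error already covers chance imbalance, and the power target is met without it. This stands.

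A reader might infer that a lopsided province could pass for a training effect. The figures do not support that: a shift of about 0.06 SD at s = 20% is small against d = 0.43 and lies within the planned SE of 0.147. Nor do the documents support a reading that the allocation is biased or the trial underpowered.

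It is also fair that the gains depend on an assumed variance share and the 42% on assumed province sizes and list order. Data analysis refers the mixed model to a statistical analysis plan that is not shown and may contain a province term. The absence of one here is therefore no omission in itself. The point rests on the stratifier and covariates that the article does state.

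On 21:21, even-sized strata with blocks chosen to close at the stratum end would give an exact split. Calling the two sections flatly contradictory would go too far; they may be condensed accounts of one scheme.

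**Conclusion.** The point holds as a low-severity, inexpensive improvement. The stated scheme is valid, unbiased and adequately powered at 0.815, but it does not use a hospital-level factor that is known in advance, in a trial where hospital-level variance is about 88% of the variance of a hospital mean. Compared with the plan, power changes by about −1 point if province explains nothing, and by about +2, +6 or +9 points if it explains 10%, 20% or 30%. These figures assume 7 hospitals per province, and the shares are illustrative because the article gives no basis for choosing among them. The 21:21 matter is a wording correction with almost no effect on power.

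**What to change.** - **If allocation has not been done:** replace the block lists with one computer draw over the 42 listed hospitals. Choose at random among allocations with exactly 21:21 overall and arms differing by at most one hospital within each hospital type and each province. Include province and hospital type as fixed effects in the primary mixed model.
- **If allocation has been done** (Setting and participants mixes past and future tense): leave it as it is and add the prespecified province and type terms only, before outcome data are seen. The benefit is then less certain. At a mean efficiency of 0.88, the province term pays on average only if it removes more than 12% of hospital-mean variance, which is s of about 0.12 × 0.2267/0.2 = 14%.
- **In either case:** make Setting and participants and Randomization and allocation concealment describe the same scheme. If block lists are kept, state the stratum sizes and whether blocks are chosen to close at the stratum end, or give 21:21 as a target.

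The cost is a short script and a few protocol sentences. Province takes 5 df, and with the 4:3 splits that is about one point of power at worst (0.815 to 0.804). The hospital type term takes one further df, which lowers the 0.804 to about 0.803 (34 df, same SE).

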### Eligibility

Inclusion criteria will be frontline doctors and nurses who voluntarily participate, agree to sign informed consent, and who are not specialized in mental health in clinical work (e.g., emergency department, infectious disease department, orthopedics department, emergency unit, etc.). All individuals who meet the inclusion criteria will be invited to participate, unless they are excluded due to previously receiving PFA training or training with overlapping content or physical illness.

### Ethical considerations

Our research will guarantee the confidentiality and safety of participants. We will not share personal information to any third parties, such as agents, employers without their consent. Informed consent will be obtained from all the participants. The researcher will provide information about the study and it’s aims to the participants before obtaining their informed consent. This study protocol has been approved by the Second Xiangya Hospital, Central South University Clinical Research Ethics Committee (2021) Ethical Review [Clinical Research] #067), and the trial protocol was registered with the China Clinical Trials Registry: ChiCTR2200060464^1^. Participants will provide written consent before the study begins. Participants can withdraw from the study at any time and for any reason without prejudice.

### Sample size

The total sample size of 1399 health care workers was estimated with a power = 0.80 and an alpha = 0.05, using PASS software based on *d* = 0.43 (12) and an ICC of 0.2 estimated in a similar study conducted in Nepal (13). The total minimum required sample size was 21 clusters per arm with 30 participants with an additional 10% inflation for drop out in each cluster to show a 20% difference in mean competency score on the psychological skills and knowledge (14) between the intervention group and control group immediately after training and at 1 and 2 month the follow-ups.

